**Outdoor play values, policy, and practice**		
	ELCC^a^ center administrators and staff identify the organization’s core values related to outdoor play, including why they value it, and how they want to support it. The values form the basis for a review of existing policies, procedures, and practices to determine whether they are aligned or require modification. Values are shared with the ELCC community, and the modified policies, procedures, and practices are implemented within the ELCC center.	Each ELCC center’s administrators and staff worked together on this activity. It was integrated into the professional learning and mentorship avenues, and also supported by a supplemental session with research team members.
**ECE^b^ Professional Learning and Mentorship**		
	Training and mentorship to build knowledge and self-efficacy around outdoor play. Ongoing mentorship to address emerging issues and build on learning.	The Learning Outside Together, Incorporating traditional wisdom and promising practices to futureproof child care (LOT) program is an already established 10-12-week program with asynchronous online modules that are paired with synchronous weekly meetings where ECEsb meet with a peer mentor [39]. LOT incorporates local, traditional Indigenous wisdom of Land as Teacher and practices related to outdoor learning in ELCC settings. A mentorship network, which includes liaisons from all participating ELCC centers, meets via web once per month to discuss details of the project, troubleshoot emerging issues, and share ideas. Indigenous centers are paired with Indigenous mentors to support cultural safety. ELCC centers participating in the PRO-ECO 2.0 study were invited to participate as their own cohort as part of the larger LOT program (which operates outside of the PRO-ECO 2.0 study).
**Outdoor Space Modification**		
	ELCC centers modify their outdoor space to increase affordances for play. Modifications include adding loose parts, plants, and other natural materials.	Environmental modifications were designed and implemented by each of the ELCC centers, with support from the research team and the Steering Committee. Each participating ELCC center was allocated the same funding to complete environmental modifications and retained considerable discretion in how to allocate these resources. Each center was provided with CAD $8800 (US $6471) for general expenses and CAD $1600 (US $1176) for shade-related components. Liaisons were given a workshop on the Seven Cs design guidelines [40] and provided with a “look-book” with ideas for outdoor space and shade modifications. The research team worked with each center to help support the development and execution of their plans.
**Family Engagement**		
	Each center plans a family engagement event in the format that most suits their families. The intention is to increase parents’ and caregivers’ knowledge of the importance of outdoor play, and encourage family involvement in implementing the outdoor space modification.	Materials and engagement activities led by ELCC centers with support, as needed, from Outside Play Lab. Examples of family engagement activities include: seed planting activity, working in garden boxes, planting seedlings, and creating beanpole teepees, sharing food with families and talking about the project, looking at info graphics and maps with data from interviews with the children.

^a^ELCC: early learning and child care.

^b^ECE: early childhood educator.

These learnings, alongside a 5 R’s research approach, were considered in the implementation of the PRO-ECO program as part of the PRO-ECO 2.0 study, as outlined in Table 2. For example, engagement events were mobilized in a format that best suited the families at each center to increase engagement opportunities that were often challenging to realize in the PRO-ECO 1.0 study. In addition, ECE training was implemented through a mentorship network over a period of 10-12 weeks to support more long-term learning and sustainable training opportunities. ELCC centers participating in the PRO-ECO 2.0 study also received financial resources to help defray the costs of participation. Each site received CAD $15,000 for staff costs (US $11,029), CSD $8800 (US $11,029) to pay for supplies and modifications to the general outdoor environment, and CSD $1600 (US $1176) from BC Cancer to cover the costs for shade-related materials. The ELCC centers were informed about the funding for staff costs after enrollment, when extra resources became available from the funding agency.

### Study Design

The PRO-ECO 2.0 study is designed as a mixed methods waitlist control cluster randomized trial. This mixed methods approach included quantitative and qualitative data collection to evaluate the effects of the PRO-ECO project, and qualitative data gathering to plan project implementation, understand children’s ECEs’ and families’ experiences with the project, and gather their perspectives on its effects.

### Inclusion Criteria and Recruitment

The PRO-ECO project was designed for ELCC centers that provide licensed full-time group child care to children aged 2.5 to 6 years. The Steering Committee decided to open the study to ELCC centers in BC that opted into the Affordable Child Care Benefit, which is a provincial government subsidy to support eligible families with the cost of child care [41], to help ensure inclusivity of lower-income families. Additionally, while we wanted to be as inclusive as possible of remote rural locations, practicalities necessitated that ELCC centers had reasonable access to a plant nursery or hardware store to be able to access material for the outdoor space modification. The definition of what was reasonable was left up to the ELCC centers to determine (eg, within a 2-hour drive).

Recruitment notices were delivered through our Steering Committee partner organizations (in newsletters or through email blasts), posted on social media, and on the Outside Play Lab website (OutsidePlay.org). While recruitment was not explicitly targeted toward Indigenous-led ELCC centers, by distributing through our Steering Committee and partner organizations, we received interest from more Indigenous-led centers than might have been the case if the notices were distributed by another, less known or trusted organization. Interested ELCC centers contacted the Outside Play Lab, and an informal meeting was planned to explain the parameters of the partnership. A secondary zoom interview, with multiple PRO-ECO steering committee and center/band representatives, to discuss readiness for partnership, participation, and particularly access to resources to support the necessary time to the project (ELCC centers could rely on volunteers, managers, Elders, or others within their community to help them meet these time commitments). Discussion questions were provided before the meeting, and ELCCs had the opportunity to respond with their items before and during the Zoom session. The meeting also offered an opportunity to introduce members of the PRO-ECO team and their roles, while touching on how management, including staff teams, boards or organizations, and community bands or municipal governments, could modify policies, practices, and outdoor play environments.

A total of 28 ELCC centers expressed their interest in participation, and of these, 12 ELCC centers were selected for inclusion. While our desired sample size (see sample size calculation below) required the recruitment of 10 ELCC centers, we selected 12 ELCC centers to account for potential center withdrawal. Indeed, 2 centers decided not to continue participation prior to baseline data collection, citing staffing challenges. Following site selection, each ELCC appointed an ELCC-PRO-ECO project liaison (“liaisons”) to connect the research team, ELCC staff, and families. ECE’s and staff at participating ELCC centers during the course of the study were recruited to participate in this study between August 2023 and October 2024.

The PRO-ECO 2.0 study included ELCC centers in 10 different communities across the South Cariboo, East Kootenay, Northern, Southern Interior, Greater Vancouver, Thompson Okanagan, and Vancouver Island regions of British Columbia, Canada. Among the 10 participating ELCC centers, 7 are located in rural locations and 3 in urban locations. In addition, 5 participating ELCC centers are operated on reserve by Indigenous-led organizations.

Children attending a participating ELCC center during the course of the study and their family members were recruited to participate in this study between September 2023 and October 2024. Recruitment of children and families occurred through each ELCC center, posting flyers and distributing letters and emails that outlined details of the PRO-ECO project and sought participation. Center staff also initiated face-to-face conversations with families during drop-off and pick-up times. Over the course of the study, participating children left or graduated from their ELCC center, and newly enrolled children were recruited as the study progressed. Parental written consent was received from participating children. All children attending the ELCC programs were exposed to the PRO-ECO program, either as group 1 or group 2, regardless of consent status.

### Randomization

Individual ELCC centers served as the unit of randomization in the waitlist control cluster randomized trial design. ELCC centers were randomized to either group 1 or group 2 prior to baseline data collection. Five group 1 centers implemented the PRO-ECO program immediately following baseline data collection, whereas 5 group 2 centers, acting as waitlist control sites, implemented the PRO-ECO program following time 2 data collection. Randomization was conducted by Steering Committee members who randomly drew 5 separate slips of paper with ELCC center names to represent group 1. The research trial coordinator was not blinded to the randomization, and ELCC centers were aware of their group during baseline data collection because planning was already underway with group 1 ELCC centers for launching the implementation of the PRO-ECO project. Data on outcome measures were collected at 3 time points: baseline (time 1), 6-month follow-up (time 2), and 12-month follow-up (time 3). Outcome data aimed to assess the short-term and longer-term outcomes within group 1 and the short-term outcomes within group 2. Data collection occurred during the fall and spring seasons to compare similar weather patterns at each data collection time point.

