### Data Analysis

We aimed to collect 512 fifteen-second video clips at each center for each time point, for a total of 5120 video clips per time point (total N=15,360). This power calculation was based on the statistically significant effect size we observed in the PRO-ECO 1.0 study related to the short-term impact of the program on improving play occurrence (time 1 vs time 2 for group 1 and time 2 vs time 3 for group 2) [23]. The key coefficient of interest is the intervention by group interaction term, which corresponds with a *R*^2^ increase of 0.00295 (ie, variance explained by the special effect), equaling to an effect size of 0.00308, when this interaction term is added to the multivariate regression model. We also expect to have 5 control variables (ie, intervention, group, weather conditions, temperature, and child gender) in the multivariate regression models, which altogether correspond with a residual variance of 0.958. This supports a power calculation of over 99% (0.997) to detect the program effect that we observed in the PRO-ECO 1.0 study. The power calculation was conducted using the G*Power software [50].

To analyze the effect of the PRO-ECO program within the PRO-ECO 2.0 study, we intend to evaluate the change in nature play behavior between pre- and postprogram. The proportion of nature play occurrences compared with nonnature play occurrences across ELCC centers at baseline will be summarized by treatment group using frequencies and percentages. This approach mirrors our analysis in the PRO-ECO 1.0 pilot study [22,23], which demonstrated the effectiveness and significance of measuring children’s outdoor play occurrences through a comparison of play and nonplay behaviors pre- and postprogram implementation. However, in contrast to the PRO-ECO 1.0 study, this study focuses on the occurrence of nature play as the primary outcome variable, and not play participation in general.

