Baseline demographic and ELCC characteristics will be summarized by group using means and SDs, medians and IQRs for continuous variables, and frequencies and percentages for categorical characteristics. Bivariable relationships between children’s demographic characteristics and outdoor nature play occurrence, both overall and by group, will be explored to identify potential confounding factors at the individual level, considering randomization occurs at the cluster level. Mixed effects models will be used to assess differences in quantitative outcome measures between groups, as well as within-group comparisons of pre- and postprogram implementation measures.

We will analyze child interviews using qualitative content analysis methods to systematically identify patterns and themes that reflect children’s perspectives and experiences on outdoor play and well-being [51]. The method’s adaptability to diverse data types and research contexts, combined with its structured and systematic analytical process, makes it particularly viable for exploring the wide-ranging and expressive nature of children’s responses. For ECE and family listening circles and interviews, we will use thematic analysis, which involves identifying and analyzing key themes within the data [52]. We will follow a reflexive thematic analysis to facilitate insights regarding ECEs’ and families’ perspectives on various interconnected topics, such as the importance of outdoor play, power dynamics, cultural norms on outdoor play, and the acceptability of the PRO-ECO program.

In alignment with the PRO-ECO project values and the partner research agreements, we will work with participating ELCC centers and the Steering Committee to share ongoing results from this study. Steering Committee members and liaisons will be invited to join a working group to work with the Outside Play Lab team on guiding and interpreting the analyses. We will gather ongoing iterative input from the broader Steering Committee and ELCC center teams to help interpret the findings, guide subsequent analyses, and develop recommendations. This form of member checking will seek to ensure all analyses and results align with the desired outputs of our project partners and appropriately convey the findings.

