## Results

This study was developed to cocreate, administer, and evaluate the PRO-ECO program following the implementation of the PRO-ECO pilot study in 2021. Funding to conduct this study was confirmed in March 2022. Ethics approval was received in September 2022. Recruitment of ELCC centers occurred from January 2023 to June 2023, followed by participant recruitment beginning in August 2023. Baseline data were collected between October 2023 and December 2023, and the group 1 ELCC centers received the PRO-ECO program from December 2023 to April 2024. Group 2 ELCC centers received the PRO-ECO between May and September 2024. Data collection was completed in March 2025. A total of 229 children were recruited to participate in the study, with 193 children participating in observational play videos for coding and 162 children participating in one-on-one interviews. Additionally, 91 staff and educators consented to participate in the study, with 59 participating in focus groups and 84 completing the T-TRiPS survey. In follow-up to consenting for their child to participate, 41 family members completed an interview or family survey to add their perspectives to the study. The PRO-ECO 2.0 waitlist control cluster randomized trial flow diagram is provided in Figure 2.

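### Group 1's change from time 1 to time 3 is uncontrolled because group 2 has crossed over by then; the longer-term effect needs a joint two-group model with a stated assumption

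*Protocol article*

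**What the plan says.** All references are to the protocol article.

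- **Aim by group (Randomization):** "Outcome data aimed to assess the short-term and longer-term outcomes within group 1 and the short-term outcomes within group 2". The waves are baseline (time 1), 6 months (time 2) and 12 months (time 3).
- **Crossover:** the five waitlist centers "implemented the PRO-ECO program following time 2 data collection" (Randomization). Results gives the dates: "Group 2 ELCC centers received the PRO-ECO between May and September 2024".
- **Children (Inclusion Criteria and Recruitment):** over the study "participating children left or graduated from their ELCC center, and newly enrolled children were recruited as the study progressed".
- **Analysis (Data Analysis):** "Mixed effects models will be used to assess differences in quantitative outcome measures between groups, as well as within-group comparisons" of measures before and after the program. The short-term impact is defined as "time 1 vs time 2 for group 1 and time 2 vs time 3 for group 2". The control variables listed with the power calculation are intervention, group, weather, temperature and child gender; time point is not among them.
- **Secondary measures (Additional Outcome Measures):** T-TRiPS, the Seven Cs ratings and the child interviews are collected at times 1 and 3 only.

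The article does not say that the longer-term result has no control group.

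**The concern.** The longer-term question is placed inside group 1, and the only analysis described that stays inside a group is a pre/post comparison. At time 3 that comparison has no concurrent unexposed centers. Anything that moved nature play between the two years is credited to the program: general year-to-year change, children leaving and joining, and familiarity with being filmed.

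The between-group comparison at time 3 does not repair this, because both groups have by then been exposed. A fully lasting effect would appear there as no difference.

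Fading could therefore be reported as persistence, and persistence as a null result. What is at stake is the longer-term aim and the secondary measures taken only at times 1 and 3. The short-term randomized result is not at stake.

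**Working it through.** **1. The plan's own figure.** Data Analysis gives an R² increase of 0.00295 and a residual variance of 0.958, so f² = 0.00295 / 0.958 = 0.00308. In a noncentral F test with N = 10,240 clips (two time points × 5,120), noncentrality is 0.00308 × 10,240 = 31.5. With 5 numerator degrees of freedom and alpha 0.05 (assumed, not stated), power is 0.997, as the article reports. The figure rests on the short-term contrasts and says nothing about time 3.

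**2. Cell means.** Let m be the group 2 baseline, g the group offset, d2 and d3 the drift from time 1 to times 2 and 3, S the short-term effect and L the longer-term effect.

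| | Time 1 | Time 2 | Time 3 |
|---|---|---|---|
| Group 1 | m + g | m + g + d2 + S | m + g + d3 + L |
| Group 2 | m | m + d2 | m + d3 + S |

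- Group 1, time 3 minus time 1 = L + d3. L cannot be separated from d3.
- Group difference in change, time 1 to time 2 = S.
- Group difference in change, time 1 to time 3 = (L + d3) − (S + d3) = L − S.
- Sum of the last two = L.

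The table uses the same S in both groups. Without that, the third line is L in group 1 minus S in group 2, which is not group 1's own fading. The assumption is therefore needed for L and also for reading L − S as fading.

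**3. Example (all values assumed).** S = 10, L = 5, d3 = +4 points.

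- Group 1 change: 5 + 4 = 9, apparently 9/10 = 90% retained; the truth is 5/10 = 50%.
- Group 2 change: 10 + 4 = 14.
- Difference: 9 − 14 = −5 = L − S. Then 10 + (−5) = 5 = L.
- With L = 10 instead: 14 − 14 = 0, although the effect has lasted fully.

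**4. False findings from the within-group test (simulation).** Assumed: 5 centers, base rate 20%, 64 videos per center and wave each scored once as nature play or not, center-by-time SD 0.03, paired t test, no lasting effect.

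| Drift (points) | Mean change | Rejection rate |
|---|---|---|
| 0 | 0 | 5% |
| 3 | 3 | 9% |
| 5 | 5 | 18% |
| 10 | 10 | 53% |

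Conversely, a fully lasting 10-point effect with drift of −10 points gives a mean change of 0.

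**5. Precision of the alternative, same assumptions.** Variance of one center-by-time proportion: 0.03² + 0.2 × 0.8/64 = 0.0009 + 0.0025 = 0.0034.

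- Group 1 change: √(2 × 0.0034/5) = 0.037.
- S, and likewise L − S: √(4 × 0.0034/5) = 0.052.
- L: weights −2, 1, 1 in group 1 and 2, −1, −1 in group 2, sum of squares 12, so √(12 × 0.0034/5) = 0.090.

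The ratio 0.090/0.037 is about 2.4. A normal 95% interval for L is about ±18 points (1.96 × 0.090), before any small-sample correction for 10 centers.

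**The case against.** The case on the other side has several parts.

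- **The sentence in Randomization describes which follow-up each group supplies; it does not name an estimator.** Partly right. But Data Analysis does plan within-group pre/post comparisons, states no control for the longer-term one, and lists no time-point term. That list accompanies the power calculation, so a fuller model may exist elsewhere. Even so, what the article describes leads to the uncontrolled contrast.
- **Loss of the control is inherent in a waitlist design, and the aim is subsidiary.** True: none of the three numbered objectives mentions longer-term effect, and power is based on the short-term effect. Answering within group 1 is still a choice, since group 2 at time 3 carries the same drift.
- **Drift is overstated.** Season is broadly matched: baseline ran October to December 2023, and Table 1 places time 3 updates in September to December 2024. Weather and temperature are covariates, child characteristics are collected, and turnover is not quantified. This removes much of the seasonal argument, but not year-to-year change, changed child mix or repeated filming. The crossover alone is enough for the point.

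Three stronger readings should be resisted. A reader might infer that the trial cannot show whether the effect lasted; the three-wave data can, under the equal-effect assumption. A reader might infer that one pooled pre/post variable forces group 1's time 2 and time 3 effects to be equal; the article does not say so, and its short-term definition leaves group 1's time 3 out. A reader might infer that the main trial result is compromised; the comparison from time 1 to time 2 is untouched.

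**Conclusion.** The concern holds in limited form. Group 1's change from time 1 to time 3 estimates L plus drift, and the between-group difference in that change estimates L − S. Neither is the longer-term effect, and the article does not warn of this. That follows from the crossover dates alone.

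The size of the bias equals the drift, which the documents do not give; the 9-versus-5 example and the rejection rates of 9% to 53% are illustrations on assumed inputs.

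The primary outcome can be repaired without new data if the short-term effect is the same in both groups. The article gives grounds for caution: the program is tailored by center (Implementation of the PRO-ECO Program), and delivery overran in some centers (Strengths and Challenges), so some group 2 centers may be only partly exposed at time 3. With five centers per group, the estimate of L may be too imprecise to settle the question.

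**What to change.** 1. **Primary outcome.** Fit one mixed model to both groups and all three waves, with time-point and group terms and separate indicators for short-term and longer-term exposure (group 1: none, short, longer; group 2: none, none, short). Report S from the group difference in change from time 1 to time 2, L − S from that from time 1 to time 3, and L as their sum.
2. **Assumption.** State that both L and the reading of L − S as fading require an equal short-term effect in the two groups, and that center tailoring and late implementation may strain it.
3. **Labelling.** Report group 1's raw change from time 1 to time 3 as descriptive and uncontrolled, and say that a time 3 group comparison is exposed versus exposed.
4. **T-TRiPS, Seven Cs and child interviews.** The recoding does not help, because there is no time 2 measurement. Label their changes from time 1 to time 3 as uncontrolled.
5. **Disclosure.** Table 1 records early results shared by March 2025, so date the change and say what had been seen.

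The cost is a few lines of analysis text and one recoded exposure variable, with no new data. The price is precision: the interval for L is about 2.4 times as wide as that for the within-group change.
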